### Eligibility

The inclusion criteria are as follows: 1) clinical diagnosis of plantar fasciitis with failure of conservative treatment including stretching exercises, nonsteroidal anti-inflammatory drugs, analgesics, and insoles for at least three months; 2) individuals of both genders who are older than 18 years and younger than 80 years; 3) the patient must be able to understand the informed consent form; 4) visual analog pain scale (VAS) score greater than or equal to three points (range from 0 to 10 points).

The exclusion criteria are patients with neuropathy, skin lesions, previous degenerative lesions of the ankle, previous surgeries of the ankle or Achilles tendon, previous allergy to sodium hyaluronate, or allergies to avian proteins, those less than 16 years of age, and patients with sequelae of fractures of the tibial pilon, ankle, or foot. In addition, patients with collagen disorders, rheumatoid arthritis, and seronegative arthritis will be excluded. Patients who are not recommended to use shockwave therapy include the following: patients who use anticoagulants, are pregnant, have a tumor in the treatment area, systemic infections or epilepsy.

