### Sample size

The sample size was calculated using the *pwr* package of R software [19]. A study by Chew et al [20] was used to determine the minimum change required in the treatment of chronic plantar fasciitis with regard to the main outcome, which will consist of a change of 3.0 points in the VAS between the baseline value and that at three months of follow-up after the intervention. The pooled standard deviation was set to 4.5 after examining preliminary values. Thus, we chose a study power of 80% and type I error of 5%. The calculated sample size was 36 patients in each group, but a sample size of 40 was specified to allow loss to follow-up during the study (10%).

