### Outcome measures

The primary outcome to be evaluated will be the VAS. The questionnaire will be administered at baseline and three, six, and 12 months after the intervention during routine visits previously scheduled with the researchers.

The secondary outcomes to be evaluated will be function and personal satisfaction. The former will be assessed based on the American Orthopaedic Foot and Ankle Society (AOFAS) score [21] for the ankle and hindfoot and the Foot and Ankle Outcome Score (FAOS) [22]. The latter will be evaluated based on the personal satisfaction criteria published by Roles and Maudsley [23].

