### Statistical analysis

Statistical analysis will be conducted primarily through an intention-to-treat analysis of all patients, in both arms, except for lost cases or withdrawal of informed consent. In addition, a per–protocol analysis will be conducted.

All analysis will be performed using the statistics package of R software [19]. We will use the repeated measures ANOVA (analysis of variance test) for the primary and secondary outcomes and also the Fisher’s Least Significant Difference, a Post-Hoc test.

Continuous variables will be measured using descriptive statistics, including the mean and standard deviation, and tested for the normality of their distribution using the Shapiro test [24]. Categorical variables will be presented according to their proportion and confidence interval.

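### Fisher's LSD after the repeated measures ANOVA has no stated contrast, error term or gate; on the within-patient residual, an ungated HA-versus-ESWT test at one visit would exceed 5%

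*Protocol article*

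**What the plan says.** The Statistical analysis section of the protocol article gives the method in one sentence: "We will use the repeated measures ANOVA (analysis of variance test) for the primary and secondary outcomes", supplemented by Fisher's "Least Significant Difference, a Post-Hoc test". On software it says only that "All analysis will be performed using the statistics package of R software"; no function is named for the LSD step.

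Four time points can enter the model: "The questionnaire will be administered at baseline and three, six, and 12 months after the intervention" (Outcome measures). That section names the primary outcome simply as the VAS. The Sample size section is more specific and sizes the trial on "a change of 3.0 points in the VAS between the baseline value and that at three months of follow-up after the intervention", with 80% power and a 5% type I error. The Statistical analysis section does not tie the LSD test to that quantity.

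The Eligibility section requires a VAS of at least 3 on the 0-10 scale at entry. No such floor applies at follow-up.

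**The concern.** LSD differs from a set of ordinary t-tests in that it borrows its standard error from an ANOVA mean square. A repeated measures ANOVA has two: one between patients, and one within patients from which the stable differences between patients have been removed. The within-patient residual suits visit-to-visit changes in the same patients. A comparison of HA with ESWT at month 3 is between different patients and needs the between-patient variance as well.

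With two arms, no post-hoc test is needed for the arm main effect. LSD is therefore useful only for comparing visits or arm-by-visit cells, and since the trial's aim is HA versus ESWT, an arm comparison at a visit is a natural use. If it were done on the residual mean square, p-values for VAS, AOFAS and FAOS would be too small, and one treatment could be declared better on intervals that are too narrow. This is separate from multiplicity: it affects a single comparison at a single visit, and adjusting for several visits would not repair the standard error.

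**Working it through.** **Inputs from the protocol article.** Difference 3.0, SD 4.5, power 80%, alpha 5% (taken as two-sided; not stated), 36 per arm raised to 40 for 10% loss, 1:1 allocation, four visits.

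**Inputs assumed.** The correlation between visits (rho) and the visit-specific SDs. The article gives neither, so results are shown over a range.

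**1. The plan's own figure.** n = 2 x (1.960 + 0.842)^2 x (4.5/3.0)^2 = 35.3, so 36 per arm; 36/0.90 = 40. Both reproduce (the exact noncentral-t calculation gives 37).

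**2. Residual mean square, arm comparison at one visit.** With equal visit variances sigma^2 and common correlation rho:

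- variance needed: 2 sigma^2 / n
- variance used: 2 sigma^2 (1 - rho) / n
- ratio of standard errors: sqrt(1 - rho)
- actual size: about 2 x [1 - Phi(t_crit x sqrt(1 - rho))]

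With 36 per arm the residual has (72 - 2) x 3 = 210 df, so t_crit = 1.971.

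| rho | SE ratio | t_crit x ratio | actual size |
|---|---|---|---|
| 0.1 | 0.949 | 1.870 | 6.1% |
| 0.3 | 0.837 | 1.649 | 9.9% |
| 0.5 | 0.707 | 1.394 | 16.3% |
| 0.7 | 0.548 | 1.080 | 28.0% |

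Simulation of 20,000 null trials per setting gave 10.0%, 16.3% and 27.8% at rho 0.3, 0.5 and 0.7 (36 per arm), with almost the same results at 40 per arm. A two-sample t-test on the month-3 values alone gave about 5% throughout.

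On the VAS scale, if 4.5 is read as the SD at one visit, the least significant difference on that visit's own variance is 1.994 x sqrt(2 x 20.25/36) = 2.12 points. On the residual at rho 0.5 it is 1.971 x sqrt(2 x 10.125/36) = 1.48 points. The size in the table does not depend on the value of the SD.

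**3. Combined split-plot error, same comparison.** The error is [MS between + 3 x MS residual]/4. Its expectation is sigma^2 x [(1 + 3 rho) + 3(1 - rho)]/4 = sigma^2, which is the right quantity. Simulated size was 4.7-5.1%, and an SD pooled over the eight arm-by-visit cells behaved the same way (4.8-5.2%).

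This error averages the four visit variances, so a smaller baseline variance pulls it down:

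- assumed SDs 2 at baseline and 4.5 later: SE ratio sqrt[(4 + 3 x 20.25)/4 / 20.25] = 0.894, size about 8%
- assumed SDs 1.5 and 2.5: SE ratio sqrt[(2.25 + 3 x 6.25)/4 / 6.25] = 0.917, size about 7%

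Simulation gave 7.1-8.0% in these settings. With other assumed SDs the range is about 5-8%.

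**4. Arm difference in change from baseline, on the residual.** Each patient's change has variance 2 sigma^2 (1 - rho), so under sphericity the residual is the correct error. Simulated size was about 5% there. Over non-spherical settings it was mostly 3-7%, with extremes of 2.0% and 7.7%.

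**5. A gate before LSD, residual error, single-visit comparison.**

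- Gate on the group-by-visit F, arms equal at every visit: 1.3-2.9%.
- Same gate, true 3-point difference at 12 months only, rho 0.5: the month-3 test, where the arms do not differ, rejects in 14%.
- Gate on the visit effect alone: essentially as high as with no gate.

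**The case against.** A reader might infer that the planned analysis as such fails to hold 5%, even for one pre-named 3-month test. The protocol article does not support that.

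- It never says the residual mean square will be used. The only thing it calls pooled is the planning SD. The error term of a post-hoc contrast is a detail that may sit in an analysis plan not shown.
- The one 3-month quantity it names is a change from baseline. For the arm difference in change, the residual is the right error under sphericity, and departures are modest.
- LSD is classically run only after a significant F test. Gated on the group-by-visit F, it is conservative when the arms do not differ at any visit.
- The article gives no correlation or visit-specific SD, so no single inflation figure can be quoted. The entry cut-off restricts VAS only, so the unequal-variance argument does not extend to AOFAS or FAOS.

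All four points stand, and they make the finding conditional. They do not remove it. The named procedure is one whose error rate depends on choices the article leaves open, and one ordinary set of those choices gives a seriously wrong test. The gate is not stated either, and it does not protect once the arms differ at another visit.

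**Conclusion.** The concern holds conditionally. If LSD takes the within-patient residual and is run ungated for HA versus ESWT at one visit, a nominal 5% test has an actual size of roughly 6%, 10%, 16% and 28% at assumed correlations of 0.1, 0.3, 0.5 and 0.7 with equal visit variances. The mechanism applies equally to VAS, AOFAS and FAOS.

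The stronger statement, that any error term drawn from this ANOVA is too small, is not correct. The combined error holds about 5% at equal variances and about 5-8% if baseline VAS varies less, and the change contrast stays at about 3-7%. What can be said is that the article fixes a method whose validity turns on an unstated contrast, error term and gate. It is worth correcting because the correction is cheap and does not depend on the unknown correlation or visit variances.

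**What to change.** For between-arm comparisons, replace Fisher's LSD with the HA-minus-ESWT difference and its 95% CI at 3 months, and likewise at 6 and 12 months, from a repeated-measures mixed model with visit-specific variances and unstructured covariance (Kenward-Roger degrees of freedom).

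If the classical ANOVA is kept, state that each between-arm contrast is computed from that visit's own variance, or from the change score's own variance, and never from the within-patient residual mean square. Apply the Greenhouse-Geisser correction to the ANOVA's visit and interaction tests.

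The cost is one sentence in the Statistical analysis section, a few lines of R, and slightly wider intervals.

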## Results

Recruitment and data collection started in November 2020. We estimate that data collection should be completed in June 2022, and the results should be available in November 2022.

## Discussion

### Overview

The present study will be unprecedented in terms of the inclusion of HA injection for the treatment of chronic plantar fasciitis in a randomized clinical trial. We believe that use of shockwave therapy in the control group can serve as a reliable parameter in comparing the results.

The possibility of comparing the results with those of corticosteroid injection seems to be the most rational, but the published results on complications related to rupture and injury of the plantar fascia contributed to the decision to not include this type of intervention in the study design [8–10].

We also chose not to include placebo therapies such as anesthetic infiltration or needling because shockwave therapy has shown satisfactory results and thus can be used as a control. The use of HA in the study group is justified because it is a new procedure for treatment of chronic plantar fasciitis, with only one case series showing benefits with its use [14].

In addition, HA has been increasingly used in the treatment of tendinopathies and extra-articular inflammation [25–27]. Other types of interventions, such as botulinum toxin injection, were excluded based on previously published results [28].

The described effects of HA include local lubrication [29], promoting tissue healing in the region between bone and tendon [30], and tissue regeneration [31]. Another important function reported is to decrease the sensitivity of regional sensory nerves, with decreasing pain [32].

The ESWT intervention produce an effect that is considered direct and other indirect on the treated region. The indirect effect is the production of localized cavity bubbles. The direct effect is the transmission of energy from the equipment to the target tissue. Both produce a local biological response [33].

This protocol describes a study focused on the application of a new treatment method to combat chronic plantar fasciitis. The results of this study will have important implications for the prescription of HA as a therapeutic option, showing whether clinical improvement occurs and comparing the results with those of an effective treatment method.

### Strengths and limitations of this study

The strengths of the study are as follows: 1) new treatment method; 2) appropriate methodological design; 3) previous publication of the protocol, thus minimizing publication bias; and 4) single-center study using the same technique, interventions, and evaluators. We believe that the main limitations of the study are the short follow-up duration and that the mean age of patients will be greater than that of the general population (our center specializes in elderly patients).

### Conclusions

This trial will evaluate the effects of a single ultrasound-guided hyaluronic acid injection for the treatment of chronic plantar fasciitis. The control group will receive an intervention using shockwave therapy, which has been shown to be effective in several previously published studies.
